#### Implementation strategies and service delivery sites

The delivery model used by a given practice depends upon their programmatic, fiscal, and resource characteristics and needs [48]. Several approaches for the delivery of behavioral health services in primary care settings have been described [49]. In this trial, we partnered with three pediatric primary care agencies that serve high rates of low-income, ethnic minority families (about 60–65% Latino; 10% African American; 5–8% American Indian). Because pediatric primary care offices often do not have integrated behavioral health, arm 1 uses a strategy of coordinated care between primary care and an external behavioral health provider. We partnered with a large outpatient general pediatrics clinic associated with a children’s hospital. We also partnered with two agencies that are part of the nationwide network of 1250 Federally Qualified Health Centers (FQHCs). A feature of FQHCs is the integrated care model that typifies the medical home. In arm 2, we will test an integrated/co-located model of care. The FQHC network is crucial for embedding a family-centered approach to care because it serves youth and families at high sociodemographic risk and is intended to integrate services to reduce barriers and improve care. Partnering with these provider sites afforded the opportunity to compare FCU4Health implementation under two different real-life service delivery models. In both arms, behavioral health consultants are responsible for delivering the FCU4Health and coordinating care with other support services and resources.

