#### Implementation

To assess the *acceptability*, *feasibility*, *appropriateness*, and *sustainability* of each component of the FCU4Health (e.g., training, program costs, content, delivery), an agency stakeholder battery will be electronically administered to at least 30 agency stakeholders (approximately ten from each agency) at two times during the study: 4 months into the FCU4Health delivery and when all families enrolled in the study complete the entire 6-month FCU4Health protocol. Families in the FCU4Health arm will rate the acceptability and appropriateness of the program via an electronically administered survey at months 6 and 12. Additionally, 20% of families in the FCU4Health arm will be randomly selected and interviewed by study staff via phone.

Study enrollment and participation data will be used to evaluate the *reach* of the program in each agency by tracking both the proportion of eligible families referred to the study and the number randomized to the FCU4Health condition that engage in the program compared with the total number of eligible families [63].

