Results of the adaptation activities are largely descriptive and involve the use of qualitative data from the CAB small group discussions to describe the process and content of adaptations to the program during the course of the trial.

#### Aim 2

In addition to the specific outcomes in aims 2a–2c, we will compare the two arms on stakeholder and caregiver acceptability using repeated-measures analysis of variance (ANOVA) to analyze scores of approximately 30 stakeholders across two time points. We have sufficient power to detect a medium effect for this analysis (*f* ≥ .32). Concerning the variance of caregiver acceptability ratings between groups or over time, we have sufficient power to detect a medium effect (*f* ≥ .28). Latent growth curve (LGC) analyses will be used to determine group differences in the trajectory over time. The estimated power for this analysis is *β* = 0.12.

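### Aim 2 plans a latent growth curve for acceptability on only two waves, reports its power as β = 0.12, and compares strategies that cannot be separated from agencies

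*Protocol article*

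**What the plan says.** Under Data analysis, Aim 2, the Protocol article compares the two delivery arms on stakeholder and caregiver acceptability by repeated-measures ANOVA, "to analyze scores of approximately 30 stakeholders across two time points" for the stakeholder part. It claims sufficient power for f ≥ .32 (stakeholders) and f ≥ .28 (caregivers). It then adds a growth model and a power statement, whose value is β = 0.12: "Latent growth curve (LGC) analyses will be used to determine group differences in the trajectory over time. The estimated power for this analysis is".

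The measurement times are under Measures, Implementation. Stakeholders, about ten from each of three agencies, are surveyed twice: 4 months after delivery starts, and once every enrolled family has finished the 6-month programme. Families in the FCU4Health arm, 200 by design, "will rate the acceptability and appropriateness of the program via an electronically administered survey at months 6 and 12".

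The Data analysis overview sets 1 − β = .80 and two-sided α = .05 for all power analyses. Under Aim 3, β = .12 appears again, there as a detectable effect on the trajectory for growth models with three or four data points.

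On how strategies are allocated, Implementation strategies and service delivery sites says: "The delivery model used by a given practice depends upon their programmatic, fiscal, and resource characteristics and needs". The referral model is used by one hospital clinic and the embedded model by two FQHCs. Only families are randomised, within each strategy arm.

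**The concern.** Four things in one short paragraph do not fit together.

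- A trajectory model is announced for an outcome with two measurement times.
- The figure offered as its power is labelled β, and no reading of it is a power that agrees with the rest of the article.
- The stakeholder effect size is given without saying whether it refers to the difference between arms or to the difference in change. With about 30 people the two have very different power.
- The arms being compared are agencies that differ in many respects besides delivery strategy.

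Evaluating the two delivery strategies is the stated purpose of Aim 2. A reader could take the growth model as a separate, adequately powered test, and could take a significant person-level result as an effect of strategy when it is a difference among three agencies.

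**Working it through.** **1. Identification with two waves.** Take one score, a linear growth model with random intercept and slope, and arm as predictor.

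- Moments: 2 means in each of 2 arms (4), plus 2 variances and 1 covariance within arm (3). Total 7.
- Parameters: intercept and slope means (2), arm effects on each (2), intercept variance, slope variance and their covariance (3), residual variance (1 if equal over waves, 2 if free). Total 8 or 9.

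The rank of the moment structure is 7, so the model is not identified: slope variance cannot be separated from residual variance. The arm difference in mean slope is identified in both versions. Fixing the residual variance at 0 leaves 7 parameters for 7 moments, and the test of arm on slope is then the arm-by-time test of the two-wave ANOVA. With three waves there are 12 moments against 8 or 10 parameters, and the model is identified.

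**2. The figure β = 0.12.**

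- As a type II error: 1 − .12 = .88, against the stated .80.
- As the power itself: 12%.
- As a standardised coefficient, by Fisher's z: power ≈ Φ(atanh(.12)·√(N − 3) − 1.96).
  - N = 200: .1206 × √197 = 1.69, power .39.
  - N = 170 (15% attrition): .1206 × √167 = 1.56, power .34.
  - N needed for .80: ((1.96 + .84)/.1206)² + 3 ≈ 543.

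The third reading assumes that nothing else explains variance. If other variables explained 30 to 60% of it, power at N = 200 would be .53 to .77. Read as an arm-by-time f, about .118 is detectable with N = 200 at a correlation of .3 between waves. The article states none of these assumptions. The same simple formula gives .61 at N = 350, so the Aim 3 value must also rest on more than a simple coefficient.

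**3. f ≥ .32 with about 30 stakeholders.** Noncentral F with 1 and 28 df, two waves, equal arms. The within-person correlation ρ is not in the article, so it is varied.

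- Arm-by-time: λ = f²·N·2/(1 − ρ). At ρ = .3: .1024 × 60/.7 = 8.78, power .82. The stated figure is therefore reproduced for this effect at about that correlation (detectable f = .313).
- Between arms: λ = f²·N·2/(1 + ρ) = 6.144/(1 + ρ).

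| ρ | λ, between arms | Power, between arms | Detectable f at .80 |
|---|---|---|---|
| 0 | 6.14 | .67 | – |
| .3 | 4.73 | .56 | .43 |
| .5 | 4.10 | .50 | .46 |
| .7 | 3.61 | .45 | .49 |

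Ten per agency means 10 against 20, not 15 against 15. For the same mean difference (d = .64), λ is multiplied by (10 × 20/30)/(15 × 15/30) = .889. The between-arm power at ρ = .5 then falls from .50 to .45.

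The caregiver figure, f ≥ .28, is not in question on person-level power: with 170 to 200 raters in equal arms it exceeds .97 for either effect at correlations 0 to .7.

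**4. Strategy and agency.** Three agencies split one against two leave 3 − 2 = 1 df for a strategy contrast judged against agency variation (critical t = 12.7). If persons are treated as independent, the actual type I error is 2·(1 − Φ(1.96/√DE)), with DE = 1 + (m − 1)·ICC. The ICC and equal agency sizes are assumptions.

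| Persons per agency (m) | ICC .01 | ICC .05 | ICC .10 |
|---|---|---|---|
| 10 stakeholders | .06 | .10 | .16 |
| 67 caregivers (200/3) | .13 | .34 | .48 |

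**The case against.** A reader might infer that the acceptability trajectory cannot be analysed at all. The article does not support that. The stated target is a group difference in trajectory, the arm difference in mean change is estimable from two waves, and the planned ANOVA already contains that test. The overview also allows multi-indicator constructs where applicable, and the caregiver acceptability form has 10 items, so a constrained or multi-indicator latent change model is possible. It is not what the Aim 2 sentence describes.

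A reader might also infer that the comparison is shown to be underpowered. That goes too far. The likeliest explanation of β = 0.12 is a detectable effect mislabelled as power, as its use under Aim 3 suggests, and the article does not give what is needed to establish the true power. The .39 holds for one simple reading only. Likewise, f ≥ .32 is not simply wrong: the article does not name the effect, and the figure works for arm-by-time. It fails only as a statement about the difference between arms.

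Non-random allocation of strategy is disclosed, and randomisation of strategy is never claimed. Under Aim 3 there is a design-effect check, with multilevel models by site or coordinator if needed. That deserves weight, but it cannot separate strategy from agency when one arm is a single agency. The inflated type I errors are illustrations under assumed ICCs, not estimates for this trial.

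**Conclusion.** The point stands in limited form. The growth model as named is not identified for a two-wave score, and the constrained version duplicates the planned ANOVA. The figure given as its power is not a power on any reading consistent with the article. These two conclusions need no outside assumption beyond a single observed score per wave. The stakeholder effect size covers the arm-by-time test at a correlation of about .3, but not the between-arm difference, where power is .45 to .67 over correlations 0 to .7. The strategy contrast is a non-randomised comparison of one hospital clinic with two FQHCs, and no person-level analysis can attribute a difference to strategy.

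This should be fixed, but it does not block the trial. BMI and body composition are compared between families randomised within strategy arm, and are untouched.

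**What to change.** In Data analysis, Aim 2:

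1. Replace the growth curve for acceptability with the arm comparison of two-wave change from the planned repeated-measures model (month 12 minus month 6 for caregivers, second minus first survey for stakeholders). If a multi-indicator latent change model is intended, name it and its constraints.
2. Delete the statement that power is β = 0.12. Give the detectable effect with its type (between-arm or arm-by-time), the number of raters, the arm sizes and the assumed correlation. For the between-arm stakeholder difference this is about f = .43 to .49 at correlations .3 to .7, with equal arms.
3. Report results by agency with intervals, and describe the contrast as one hospital clinic against two FQHCs, not as an effect of delivery strategy.

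The cost is wording only: no new data and no change in sample size. What is given up is an inference about delivery strategy that three agencies cannot support.

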### Data analysis

#### Overview

Analyses focus on implementation data from the families randomized to the FCU4Health. Data from families receiving services as usual will be used in aims 2b and 3. Before data analysis, we will test the psychometric properties (i.e., distribution, reliability) of the measures, conduct a sequence of nested multiple-group confirmatory factor analyses [76] to ensure measurement invariance across language and ethnicity, and apply state-of-the-science data reduction techniques (confirmatory factor analysis, weighted regression scores) by creating multi-indicator, multi-informant construct variables when applicable. These techniques improve measurement properties and result in fewer contrasts, reducing type I error [77]. We expect the attrition rate across waves to be 10–15% based on retention rates for local studies with highly mobile, hard-to-track samples [78, 79]. We will adjust for missing data due to attrition using multiple imputation [80] and full information maximum likelihood [81]. We will perform sensitivity analyses to check the non-response mechanism [82] and attrition analyses to detect differential attrition rates and attrition by group interaction on sociodemographic and pretest variables that may pose a threat to the validity or the equity of the findings [83]. When missingness is not ignorable, we will use complex models to obtain parameter estimates [84]. To estimate power, we used Optimal Design [85] and Monte Carlo simulations in Mplus [84] and referred to relevant publications. All power analyses used 1 − *β* = .80 and *α* = .05 using two-tailed tests. For mediation models, we applied simulation in Mplus for estimating the power of path coefficients and referred to a work by Fritz and MacKinnon [86] for examining significance of mediation effects.

For qualitative data analysis, stakeholder and caregiver interviews and CAB discussions will be audio recorded, transcribed, and then coded using a directed content analysis approach [87] by using existing theory, prior results, and empirical frameworks to develop a coding scheme. Codes will be refined using a subsample of interviews, and then a team of trained coders will code full transcripts. Twenty percent of interviews will be double coded in order to calculate reliability [88]. Disagreements in coding will be resolved via consensus.

#### Aim 1

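### Aim 2 plans a latent growth curve for acceptability on two ratings per rater, which is not identified without unstated constraints, and reports its power as β = 0.12, which is not a power

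*Protocol article*

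**What the plan says.** Under Measures, Implementation, the stakeholder battery goes to at least 30 people, "approximately ten from each agency) at two times during the study". For caregivers, "Families in the FCU4Health arm will rate the acceptability and appropriateness of the program via an electronically administered survey at months 6 and 12".

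Under Data analysis, Aim 2, the two delivery strategies are compared on stakeholder and caregiver acceptability by repeated-measures ANOVA, "to analyze scores of approximately 30 stakeholders across two time points". Detectable effects of f ≥ .32 (stakeholders) and f ≥ .28 (caregivers) are given. Then: "Latent growth curve (LGC) analyses will be used to determine group differences in the trajectory over time". And: "The estimated power for this analysis is *β* = 0.12". No sample size, number of waves, constraint or definition of β goes with this.

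The Data analysis Overview has a sentence beginning "All power analyses used 1" that sets 1 − β = .80 with two-sided α = .05 throughout. It also limits the use of services-as-usual data to Aims 2b and 3, and expects 10–15% attrition.

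**The concern.** The growth-curve sentence sits in a paragraph whose only outcomes are the two acceptability ratings. The fidelity growth curve has its own paragraph (Aim 2a) with three sessions per family, and the Aim 3 growth models have three or four waves. Only this growth curve has two.

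Two waves cannot separate true between-person differences in change from measurement error, so the usual model has more unknowns than the data can supply. The figure attached to it cannot be a power, and it suggests that a small effect is detectable in a sample of at most 200 families or about 30 stakeholders.

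Comparing the delivery strategies is the purpose of Aim 2. If readers believe that a small difference could have been found, a non-significant result may be taken as equal acceptability.

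**Working it through.** **Inputs.** Two ratings per stakeholder and two per caregiver (Measures, Implementation). About 30 stakeholders, roughly ten from each of three agencies: one hospital clinic (referral) and two FQHCs (integrated), hence about 10 v 20. At most 200 FCU4Health families (Study participants, recruitment, and randomization), or 170–180 after 10–15% attrition. Power .80, two-sided α = .05, so z-sum = 1.96 + 0.84 = 2.80. The caregiver split between strategies is not stated; 1:1 and 1:2 are assumed below.

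**1. Identification.** Code the two occasions 0 and 1, with intercept variance ψ00, slope variance ψ11, covariance ψ01 and residual variances θ1, θ2.
- Var(y1) = ψ00 + θ1
- Cov(y1, y2) = ψ00 + ψ01
- Var(y2) = ψ00 + 2ψ01 + ψ11 + θ2

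That is three equations for five unknowns, or four if θ1 = θ2. With the two means, there are 5 moments against 6–7 parameters. Adding strategy as a predictor gives 7 moments against 8–9 parameters, and the Jacobian rank is 7 in both cases, so the model is not identified. Fixing the residual variances at zero gives 7 against 7: just identified, with no test of fit. With three waves (12 moments, at most 10 parameters) or four (18, at most 11) every variant is identified.

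The mean part is different. Mean intercept, mean slope and the strategy effect on each are identified even with two waves. The strategy difference in mean slope is the difference in mean change, which is the strategy-by-time term of the planned ANOVA.

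**2. The plan's figure, read three ways.**
- *As a power:* 12%, against the stated .80.
- *As a type II error:* 1 − .12 = 88%, also against .80.
- *As a standardised effect:* this is how β is used for detectable effects in Aims 2a, 3 and 4. Aim 3 pairs β = .12 with η² of at most 2%, and .12² = 1.4%.

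For the third reading, a correlation approximation without covariates gives power = Φ(atanh(.12)·√(N − 3) − 1.96), with atanh(.12) = .1206, and a smallest detectable effect at 80% power of tanh(2.80/√(N − 3)).

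| N | Power for .12 | Detectable effect at 80% |
|---|---|---|
| 30 | about 10% (9.1% upper tail, 9.6% both) | .49 |
| 170 | 34% | .21 |
| 180 | 36% | .21 |
| 200 | 40% | .20 |
| 350 | 61% | .15 |

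For N = 200: .1206 × √197 = 1.69; 1.69 − 1.96 = −0.27; Φ = .40. Reaching 80% for .12 needs N = (2.80/.1206)² + 3 ≈ 543. At N = 200, covariates would have to explain 1 − .12² × 200/2.80² ≈ 63% of the outcome variance.

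**3. The contrast that two waves support.** In SDs of change, d = 2.80·√(1/n1 + 1/n2):
- caregivers 100 v 100: .40; 67 v 133: .42
- after attrition, 90 v 90: .42; 85 v 85: .43; 57 v 113: .46
- stakeholders 10 v 20: 1.09

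**The case against.** A reader might infer that the comparison of change between strategies cannot be made at all. The documents do not support that. The difference in mean change is estimable from two ratings, a constrained model is identified, and a multi-indicator latent change model is conceivable for the ten-item caregiver form, since the Overview foresees multi-indicator constructs where applicable. The mixed model recommended below is itself a growth model with slope variance fixed at zero and equal residual variances. All of this stands. It narrows the point to an unstated constraint and a redundant model, and it confirms that the growth curve cannot be more sensitive to this contrast than the ANOVA.

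A reader might also infer that .12 was carried over from Aim 3, where the same number appears for 350 families and more waves. That is possible, but nothing in the article says so.

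The percentages rest on a proxy. The authors used Optimal Design and Mplus simulation, and the same approximation gives only 61% for .12 at N = 350, so it does not reproduce their Aim 3 figure either. The metric matters too. As a repeated-measures f, in SDs of a single rating, the detectable interaction with 200 families in two equal groups is about .118 at an assumed within-rater correlation of .3. That is the same effect as above: 4 × .118/√(2 × .7) = .40 SD of change. But the plan writes β here, reports f separately, and gives f ≥ .28 for caregivers. So the approximation shows that the figure is unsupported as stated, not what the authors' simulation would give.

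Finally, the article already plans multiple imputation and full information maximum likelihood, so handling of missing ratings is no argument for the change.

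**Conclusion.** Wrong as written, on a secondary implementation comparison. The ordinary linear growth curve is not identified with two ratings, no constraint is stated, and any simple constrained form returns the ANOVA's strategy-by-time contrast. This is a stated model and a stated figure that do not fit the design, not detail left to another document.

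The power sentence fails both as a power and as a type II error. As a standardised effect it is well below what the sample can detect: about 40% power at best for caregivers and about 10% for stakeholders. Those sizes assume no covariates and a correlation approximation; the d values for caregivers also assume a split between 1:1 and 1:2. BMI, body composition and the trial's sample size are untouched.

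**What to change.** Replace the growth-curve sentence for acceptability by the strategy-by-time contrast from a linear mixed model on the two ratings, with time, strategy, their interaction and a random rater effect.

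Replace β = 0.12 by the effect detectable at 80% power for this sample, recomputed with the authors' own tools. State the metric, N, number of waves and split between strategies, separately for caregivers and stakeholders. The figures to expect are roughly .20–.21 for 170–200 caregivers (d about .40–.46 in SDs of change) and .49 for 30 stakeholders (d about 1.1 for 10 v 20). They are a guide and should not be copied into the plan unchecked.

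The cost is wording and one power calculation, with no new data or visits. The stated sensitivity becomes less favourable.

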#### Aim 2a: fidelity

We will calculate the mean score, interrater correlation coefficient, and internal consistency of the observational ratings. Using a mixed-effects model with random effects for families and a fixed-effects model, we will compare scores from prior FCU trials [53–55, 89] (Smith JD, Dishion TJ, Rudo-Stern J, Stormshak EA, Brown K, Ramos K, Thornton N, Shaw DS, Wilson MN, , A quasi-experimental study of the sensitivity and efficiency of observationally assessing fidelity, submitted) to those from the current trial. We have power to detect a small effect of *d* ≥ .18. Second, we will use the LGC analysis to (1) evaluate drift in fidelity [53] (power to detect a small effect of *d* ≥ .16 for *μ*_slope_) with the sample size of 80 families and 240 feedback sessions and (2) assess the relation between variability in fidelity on program effects (power to detect a small effect of *β* ≥ .10 for *μ*_slope_ on outcomes). To evaluate fidelity using automated coding, we will conduct the same analyses as above but with all 600 feedback sessions. Even when controlling for imperfect reliability, we have power to detect a small effect of *d* ≥ .10 for comparison to previous trials, a small effect of *d* ≥ .11 for *μ*_slope_, and a small effect of *β* ≥ .08 for *μ*_slope_ on outcomes.

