We will assess the *fidelity* of coordinators to the FCU4Health using an established observation rating system that defines high-quality care and was associated with clinical improvement in studies of the original FCU [53, 54]. A trained coding team will code video or audio recordings of the first FCU4Health feedback session from every family (*N* = 200), and a subset of 80 families will be randomly selected at study entry, balanced by coordinator, for longitudinal coding of all three FCU4Health feedback sessions to assess drift (*N* = 160 additional sessions). In addition, we will develop an automated coding system based on an existing, validated automated coding system for motivational interviewing. Automated fidelity coding will be built from previous methodologies developed for coding fidelity to MI (presence of complex reflections, open-ended questions) [56, 64, 65] and family interventions [66, 67]. Machine-generated fidelity codes have been found to be reliable with human coding across multiple studies [56, 64–66, 68, 69]. Initial algorithm training will use existing FCU feedback session recordings and the FCU fidelity codebook. Automated coding involves a computational “pipeline” of both speech signal processing and machine learning of the audio recordings of the conversations during the sessions, including (1) voice activity detection, (2) diarization (i.e., how many speakers are in session and when is each talking?), (3) role identification (i.e., who is the provider?), (4) automatic speech-to-text transcription, and (5) machine learning models to predict fidelity codes, using lexical (i.e., words) and paralinguistic features as inputs.

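### The human-coded drift model is stated on 80 families and 240 sessions; using all 360 coded sessions would estimate the fidelity slope somewhat more precisely at no coding cost

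*Protocol article*

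**What the plan says.** In the Measures part of the protocol article (Implementation), the plan for human ratings has two layers. First, "A trained coding team will code video or audio recordings of the first FCU4Health feedback session from every family", given as 200 families. Second, "a subset of 80 families will be randomly selected at study entry, balanced by coordinator, for longitudinal coding of all three FCU4Health feedback sessions", given as 160 additional sessions and described as serving to assess drift.

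Data analysis, Aim 2a, then sets the latent growth curve analysis of drift "with the sample size of 80 families and 240 feedback sessions", with a detectable mean slope of d ≥ .16. The same paragraph plans a mean score, reliability statistics and a comparison with prior trials of the original program, and does not limit these to the 80 families. It also repeats the analyses with automated codes on all 600 sessions, with a detectable slope of d ≥ .11.

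The Data analysis Overview states "All power analyses used 1 − *β* = .80 and *α* = .05 using two-tailed tests". It names multiple imputation and "full information maximum likelihood" for missing data, but only for data lost to attrition.

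**The concern.** The drift model has a named sample and a power figure attached to it, so this is a stated choice and not a detail left open. That sample omits 120 ratings that the study will already have paid to code. The 120 families lack human ratings of sessions 2 and 3 because of a random draw, not because of anything about the families. A likelihood-based growth model can use such incomplete records: they sharpen the estimated session-1 mean and, through it, the mean slope. At stake is some precision in the estimate of fidelity drift. The clinical outcomes are not affected.

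**Working it through.** **Counts.** Human-coded sessions: 200 + 160 = 360. Drift sample: 80 × 3 = 240. Left out of the drift model: 360 − 240 = 120, all first sessions.

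**Inputs from the article.** Two-sided α = .05 and power .80, so the multiplier is 1.960 + 0.842 = 2.802. Feedback sessions follow the assessments at months 1, 3 and 6.

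**Assumptions, because the article gives no figure.** The within-family correlation ρ between sessions is ranged from 0 to .9. The slope is read as change per session in units of the single-session SD, with equal correlation between sessions (compound symmetry). Attrition is not applied, since the 240 sessions are stated as complete.

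**Reproducing d ≥ .16.** With equally spaced sessions (0, 1, 2) and 80 complete families, the precision (1/variance) of the mean slope is 160/(1 − ρ). Setting 2.802 × √[(1 − ρ)/160] = .16 gives ρ = 1 − 160 × (.16/2.802)² ≈ .48. The stated figure is therefore attainable, but only through a correlation that the article does not give. At ρ = .5 the formula gives .157.

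**Adding the 120 first-session ratings.** The information for intercept and slope gains 120 on the session-1 term. The slope precision becomes

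160/(1 − ρ) + 120A/(A + 120), where A = 240/(1 + 2ρ).

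At ρ = .478: 160/.522 = 306.5; A = 122.7; added term 120 × 122.7/242.7 = 60.7; total 367.2. The SE falls from 1/√306.5 = .0571 to 1/√367.2 = .0522, which is 8.6%. The detectable d falls from .160 to 2.802 × .0522 = .146. Power at d = .16 rises from 80% to about 87%. The equivalent number of complete families is 80 × 367.2/306.5 ≈ 96.

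| Assumed ρ | Precision, 80 families | Added by the 120 | SE reduction, equal spacing | SE reduction, months 1, 3, 6 | Equivalent complete families, equal spacing |
|---|---|---|---|---|---|
| 0 | 160.0 | 80.0 | 18.4% | 16.4% | 120 |
| .3 | 228.6 | 66.7 | 12.0% | 10.6% | 103 |
| .478 | 306.5 | 60.7 | 8.6% | 7.6% | 96 |
| .5 | 320.0 | 60.0 | 8.2% | 7.2% | 95 |
| .7 | 533.3 | 54.5 | 4.8% | 4.1% | 88 |
| .9 | 1600.0 | 50.0 | 1.5% | 1.3% | 82 |

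The months 1, 3, 6 column comes from the same generalized least squares information with those times, where the simple formula above does not apply.

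**Random slopes.** Six covariance structures were tried with equal spacing; the SE reduction ran from 0% to 10.4%. The nil case can be seen directly. The slope from complete families is (third − first)/2, and its covariance with the first rating is (2 × intercept–slope covariance − residual variance)/2. With covariance .25 and residual variance .5 this is zero, so extra first sessions add nothing. That structure (intercept variance .5, slope variance .15) implies an intercept–slope correlation of .25/√(.5 × .15) = .91, which is extreme.

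None of these calculations includes a coordinator term.

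**The case against.** The strongest defense is that design and analysis agree: the 80 families were drawn to assess drift, and drift is assessed on them. A random subset gives an unbiased slope, and a detectable effect is stated. All of this stands, so no error or contradiction is shown.

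A reader might infer that the 120 ratings are thrown away. The article does not support that: nothing bars them from the mean score, reliability or prior-trial comparison. A reader might also infer that a third of the information on drift is lost, since 120/360 is one third. That is wrong too, because a single rating carries no within-family change and helps only through the session-1 mean.

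The stated sample could be read merely as the basis for the power figure. That is possible, but the text then gives no other sample for the human-coded drift model.

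The repeat on all 600 automated codes, with d ≥ .11, promises more precision than this change would. That is a fair point. However, the automated system is still being developed (Implementation; Study status), and the human-coded analysis should not depend on it.

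Finally, the draw is balanced by coordinator. If that means equal numbers per coordinator while caseloads differ, the 120 families have a different coordinator mix, and simple pooling could shift the session-1 mean and the slope. This stands as a condition on the fix. It is also true that the Overview adopts full-information likelihood for attrition only, so its use for planned missingness would have to be stated.

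**Conclusion.** The concern holds as a point of efficiency. The human-coded drift model, as stated, omits 120 usable first-session ratings. Under compound symmetry, including them would lower the slope SE by about 11–12% at ρ = .3, 7–8% at .5, 4–5% at .7 and 1–2% at .9, and the gain may be nil under some random-slope structures. At the ρ of about .48 that reproduces the plan's figure with equal spacing, the detectable d moves from .160 to about .146.

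The size rests on a correlation, a covariance structure and a slope scale that the article does not state. It would be tempting to conclude that the 80-family slope is biased or that d ≥ .16 is wrong. Neither follows: the subset is random, and .16 is reached at a plausible correlation. The point concerns a secondary implementation aim, and no clinical conclusion depends on it.

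**What to change.** In Aim 2a, state that the human-coded drift model is fitted to all 200 families and 360 sessions by full-information maximum likelihood, with sessions 2 and 3 missing by design in 120 families and coordinator, the balancing factor, in the model. Restate the sample and the detectable slope together with the within-family correlation assumed. Keep the 80-family, 240-session fit as a sensitivity check.

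The cost is a few lines of text and a rerun of the power calculation, with no extra coding. The one small downside is that, if coordinator caseloads differ, validity depends on conditioning on coordinator, which the 80-family sensitivity check helps to guard.
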